#### Key informants

In-depth qualitative interviews were conducted with consenting key informants using semi-structured interview guides (38) that were tailored for each key informant group. Interviews were audio recorded, transcribed verbatim, and translated from Sesotho to English. Acceptability, preferences, and utilization of intervention components were explored among ART initiators. Reasons for the lack of or late initiation of ART were explored among ART non/late initiators. Experiences delivering the intervention, perceived barriers and facilitators, perceptions about acceptability, and the ease of uptake and delivery of the intervention components were explored among health care workers.

#### Cost drivers

RA administered cost surveys to nurses and VHW on a monthly basis to capture the program costs associated with CIP implementation.

#### Process documentation

Several instruments were also completed by study staff to document the implementation process. A brief semi-structured *Program Characteristics Survey* was administered by the RA to the nurse in charge at each clinic in both study conditions, prior to study implementation, and on a monthly basis thereafter. The survey tracked the implementation of intervention components to assess fidelity, potential contamination, as well as system-level factors that may impact CIP implementation. At each CIP site, the RA also completed an intervention receipt log for mobile airtime, SMS messages, and transportation reimbursement to document the dosage of intervention components received by each patient, and the program monitor completed a supervision checklist during each mentorship visit to assess intervention quality (39).

Copies of data collection instruments are available from the corresponding author upon request.

### Data management

Data for participant interviews and chart abstractions were collected on paper-based forms. Completed forms were stored in a locked filing cabinet at each clinic site, and on a weekly basis were transported in a locked box to a field study office for entry in the study database. The database was encrypted, password-protected, and contained established quality control measures, including skip patterns, range limitations, and consistency checks to enhance the accuracy and completeness of the data collected. The database was backed up nightly to an encrypted external hard drive maintained in a locked filing cabinet.

Throughout the study, four levels of review were conducted to ensure the completeness and accuracy of the study data. First, the study coordinator conducted random checks of 10% of the completed study forms for errors and completeness. Second, the data manager conducted a random verification of 10% of the records newly entered into the study database against the paper data collection forms. Third, during external monitoring visits, the project coordinator reviewed 10% of the data collection forms entered into the study database for completeness and accuracy, comparing data collection forms with source documentation and hardcopy forms with the study database. In addition, the data analyst ran code to check for missing data and inconsistencies and flagged problematic observations for the study team to verify against paper-based study forms or with source documentation at the study site.

### Primary and secondary endpoints

Primary outcomes include: 1) ART initiation, 2) ART retention, and 3) TB treatment success. Secondary outcomes include: 1) time to ART initiation, 2) ART adherence, 3) change in CD4+ count, 4) sputum smear conversion, 5) TB treatment adherence, 6) cost-effectiveness, and 7) acceptability. All outcomes pertain to the individual participant level. ART initiation is defined as the percentage of TB/HIV patients newly registered during the period of observation who initiated ART during TB treatment, based on review of clinic records. ART retention is defined as the percentage of measurement cohort participants who attended their 6-month clinic visit (within a 1-month window) and reported ART use. Deaths and transfers will be considered not retained. TB treatment success is defined as the percentage of TB/HIV patients whose TB treatment outcome is documented in the TB register or treatment card as treatment completion or cure, as defined by the WHO (40). Time to ART initiation will be expressed as the number of days from TB treatment initiation to ART initiation. Adherence is determined separately for ART and TB treatment and defined by the percentage of total prescribed doses ingested, averaged across medicines for each month of treatment, from the unannounced pill counts. Change in CD4+ count is defined as the difference in CD4+ count 6 months after TB treatment initiation. Sputum smear conversion is defined as the percentage of smear positive pulmonary TB cases that converted to smear negative after 8 weeks of treatment (40). Incremental cost-effectiveness will be estimated as the ratio of the incremental costs of the CIP per ART initiation, retention, and TB treatment success. Acceptability of intervention components will be characterized via in-depth qualitative analysis and interpretation (41). Table 2 lists the study outcomes for each group of participants.

**Table 2 T0002:** Study outcomes

Study outcome	All TB/HIV patients	Measurement cohort	Key informants – ART early initiators	Key informants – ART non/late initiators	Key informants-health care workers
ART initiation^a^	X				
ART retention^a^		X			
TB treatment success^a^	X				
Time to ART initiation	X				
ART adherence		X			
Change in CD4+ count		X			
TB treatment adherence		X			
Sputum smear conversion	X				
Incremental cost-effectiveness		X			
Acceptability of intervention components			X	X	X
Reasons for ART non/late initiation				X	

a Primary outcomes.

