**Fig. 1 F0001:**
[figure not shown]
Study Participants. *All newly registered TB/HIV patients* at study sites in both conditions are represented by the large circle; those who initiated ART during the first 2 months of TB treatment (ART early initiators) are depicted in blue, while those who did not initiate ART or initiated ART after the first 2 months of TB treatment (ART non/late initiators) are depicted in green. A sample of ART early initiators from study sites in both conditions who enrolled in the *measurement cohort* are represented by the yellow circle. Key informants at CIP study sites included: 1) *ART early initiators (I KI)*, depicted by the white circle; 2) *ART non/late initiators (NI KI)*, depicted by the pink circle; and 3) health care workers *(HCW KI)*, depicted by the orange circle.

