#### All newly registered TB/HIV patients

Routinely collected data were abstracted for all TB/HIV patients newly registered for TB treatment at the 12 study clinics during the first 24 months of observation.

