### Sample size and power calculations

Power calculations for all TB/HIV patients were based on our primary outcomes ART initiation and TB treatment success. Based on previous programmatic data, we anticipated an average of 100 newly registered TB/HIV patients at each of the 12 study clinics over the first 24 months of observation. When the study was designed, available data demonstrated that only 27% of HIV-infected TB patients in Lesotho had received ART, and the TB treatment success rate was 70% for new smear positive cases, 64% for new smear negative and extrapulmonary cases, and 62% for retreatment cases (HIV-positive and HIV-negative cases combined) (42). Assuming a two-sided Farrington & Manning Likelihood Score Test with *α*=0.05 and an intra-cluster correlation coefficient (ICC) of 0.05, we will have 83% power to detect a difference in ART initiation from 40% (SOC) to 60% (CIP), and 91% power to detect a difference in TB treatment success from 65% (SOC) to 85% (CIP) (PASS 2008, NCSS Statistic Software). As per standard practice, patients who die or are lost to follow-up before ART initiation or TB treatment completion are considered to have not initiated ART or to have not achieved TB treatment success, respectively, and thus power calculations for these outcomes do not include an allowance for attrition.

Power calculations for measurement cohort participants were based on our primary outcome ART retention. Assuming 100 TB/HIV patients in each of the 12 study clinics, 40% ART initiation at SOC clinics, and at least 80% study enrollment, we aimed to enroll 384 participants (32 per clinic) initiating ART in the measurement cohort. Assuming a two-sided Farrington & Manning Likelihood Score Test with *α*=0.05 and ICC of 0.05, we will have 87% power to detect a difference in ART retention from 70% (SOC) to 90% (CIP).

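### The ART-initiation endpoint keeps patients already on ART in its denominator, although they can never enter its numerator

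*Protocol article*

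**What the plan says.** Primary and secondary endpoints gives the definition: "ART initiation is defined as the percentage of TB/HIV patients newly registered during the period of observation who initiated ART during TB treatment". Table 2 assigns this outcome, and time to ART initiation, to all TB/HIV patients.

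The section on all newly registered TB/HIV patients sets no condition on ART status: "Routinely collected data were abstracted for all TB/HIV patients newly registered for TB treatment at the 12 study clinics". The Fig. 1 caption divides that population into two classes. One is patients who started ART in the first 2 months of TB treatment; for the other it says "those who did not initiate ART or initiated ART after the first 2 months of TB treatment (ART non/late initiators) are depicted in green". Patients whose ART began before TB treatment have no class of their own.

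The secondary outcome has the same population and a fixed origin: "Time to ART initiation will be expressed as the number of days from TB treatment initiation to ART initiation".

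The article does give rules for other awkward cases. Under Sample size and power calculations, "patients who die or are lost to follow-up before ART initiation or TB treatment completion are considered to have not initiated ART". Under Data analysis, transfers before ART initiation are censored and death before ART initiation is a competing risk. There is no rule for prior ART.

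**The concern.** A patient already taking ART at TB-treatment start cannot start it during TB treatment. The intervention therefore cannot change that patient's result on this primary outcome, in either arm. Three things follow from the definition as worded.

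- The arm difference in the proportion is averaged over some patients in whom no difference is possible, so the risk difference and odds ratio shrink.
- If the share already on ART differs between arms, which chance can produce with only 12 randomised facilities, that difference passes straight into the primary comparison.
- Time from TB-treatment start to ART start is negative or undefined for these patients, so they cannot properly enter the frailty model. Dropping them there but keeping them in the proportion would give the two outcomes different populations, contrary to Table 2.

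**Working it through.** **Inputs.** From Sample size and power calculations: 12 clinics averaging 100 patients, ICC 0.05, two-sided alpha 0.05, 40% (SOC) versus 60% (CIP), stated power 83%. Assumed: 6 clinics per arm (the split is not stated), and a share f already on ART, equal in both arms. The article does not give f. Its only related figure is that, when the study was designed, 27% of HIV-infected TB patients in Lesotho had been given ART. That counts any ART, so it is a rough national ceiling for f at design. I use f = 10% and 20%.

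**Reproducing the stated power.** Design effect = 1 + (100 − 1) × 0.05 = 5.95. Effective n per arm = 600 / 5.95 = 100.84. SE = √[(0.4 × 0.6 + 0.6 × 0.4) / 100.84] = 0.0690. z = 0.20 / 0.0690 = 2.899. Power = Φ(2.899 − 1.960) = 0.826. The pooled-variance version gives 0.816. Both agree adequately with 83%.

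**Literal definition, taking 40% versus 60% to hold among patients not on ART.** Each rate becomes (1 − f)p; cluster size stays at 100.

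| f | SOC vs CIP | Risk difference | Odds ratio | Risk ratio | z | Power |
|---|---|---|---|---|---|---|
| 0 | 40% vs 60% | 20 points | 2.25 | 1.5 | 2.899 | 0.826 |
| 10% | 36% vs 54% | 18 points | 2.09 | 1.5 | 2.612 | 0.743 |
| 20% | 32% vs 48% | 16 points | 1.96 | 1.5 | 2.351 | 0.652 |

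The pooled version gives 0.732 and 0.642 at 10% and 20%. Scoring these patients as successes instead gives the same risk difference and the same pooled power.

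**Denominator restricted to patients not on ART.** Rates stay at 40% versus 60%; cluster size is 100(1 − f); ICC held at 0.05.

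- f = 10%: design effect 1 + 89 × 0.05 = 5.45; effective n 540 / 5.45 = 99.08; z = 2.873; power 0.820.
- f = 20%: design effect 1 + 79 × 0.05 = 4.95; effective n 480 / 4.95 = 96.97; z = 2.843; power 0.811.

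With an ICC of 0.05, smaller clusters cost little.

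**The other reading: 40% versus 60% describes all registered patients.** The full-denominator calculation is then the plan's own, and 83% stands. The implied rates among patients not on ART are p / (1 − f): 44% versus 67% at f = 10%, and 50% versus 75% at f = 20%.

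**Imbalance with no true effect.** Let 40% of patients not on ART start it in both arms, with f = 10% in SOC and 20% in CIP.

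- Counted as not initiated: 0.4 × 0.9 = 36% versus 0.4 × 0.8 = 32%, so CIP looks 4 points worse.
- Counted as initiated: 10% + 36% = 46% versus 20% + 32% = 52%, so CIP looks 6 points better.
- Restricted: 40% versus 40%.

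**The case against.** The strongest reply is that this is a condensed article and that handling of prior ART could sit in the full protocol or analysis plan. That would answer a complaint of missing detail. It does not fully answer this one, because the article states the numerator, the denominator and the population, and those together produce the problem.

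A reader might infer that the protocol instructs that patients already on ART be scored as failures. It does not. That is the literal consequence of the definition; the explicit not-initiated rule covers only death and loss to follow-up. Under Key informants, non/late initiators must be ART-naïve or have started ART at least 2 months into TB treatment, so the one operational definition of that group leaves prior-ART patients out. That criterion governs interviews, not the endpoint, but it counts against reading Fig. 1 as a deliberate classification.

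A reader might also infer that the 83% is wrong. It is not. The article states "we anticipated an average of 100 newly registered TB/HIV patients at each of the 12 study clinics over the first 24 months of observation" and applies 40% versus 60% to those patients. It also uses all 100 for the cohort target: 100 × 40% × 80% = 32 per clinic. The power loss appears only if the rates are re-based to patients not on ART. Shares well above 27% would give more dramatic losses, but the article offers no support for them, nor for any statement about how the share varies by site.

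Finally, being on ART by any route during TB treatment is a legitimate coverage question for an implementation trial. That stands, but it is not the endpoint as worded, which requires initiation.

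**Conclusion.** The point holds as a flaw in the endpoint definition, not as an arithmetic error. Patients already on ART are in the denominator, cannot be in the numerator, and have no meaningful value for time to ART initiation.

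The dilution affects the risk difference and odds ratio; with equal shares in the two arms the risk ratio is unchanged. Its size is conditional on two things the article does not settle: the share already on ART, and the population to which 40% versus 60% refers. The loss from about 83% to 74% and 65% is therefore a scenario, not an estimate of the trial's power.

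The exposure to imbalance does not depend on the second assumption. A 10-point difference in share gives a spurious difference of 4 to 6 points, whose sign depends on a scoring choice the article does not state. This warrants a change, though it does not invalidate the trial.

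**What to change.** Define ART initiation and time to ART initiation among newly registered TB/HIV patients not on ART at TB-treatment start, identified by the recorded ART start date. The ART registers and HIV care cards were already abstracted (Data collection), so no new source should be needed. Report the number already on ART by arm and by site. Keep all registered patients for TB treatment success. State which population the 40% and 60% refer to.

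The Trial status section puts completion of record abstraction in March 2016, and study staff were not blinded. This is therefore a change to a primary endpoint after data collection: document it, with its reason, before analysis, and report the all-registered denominator as a sensitivity analysis.

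The cost is an amended definition, a filter in the code and one extra analysis. The downsides are a somewhat smaller denominator and reliance on recorded ART start dates, which may be incomplete in routine records.

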#### Measurement cohort

In addition, a measurement cohort of TB/HIV patients initiating ART was recruited. Inclusion criteria were 1) HIV-infected; 2) on TB treatment; 3) initiated ART within 2 months of TB treatment initiation; 4) aged 18 or older; 5) English- or Sesotho-speaking; and 6) capable of and willing to provide informed consent within 3 working days of ART initiation. Patients with multidrug-resistant TB were excluded from the measurement cohort.

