### Recruitment

#### Measurement cohort

Nurses were asked to inform TB/HIV patients initiating ART about the study and to refer them to the research assistant (RA) if they were interested in obtaining more information. To achieve steady enrollment across study arms, a monthly enrollment quota was set for each site and, consecutively, eligible consenting patients were enrolled until the target number of participants was reached.

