### Data analysis

An intent-to-treat analysis will be used. In addition, when measuring adherence in the measurement cohort, an as-treated analysis will be used to exclude participants who died or discontinued medications due to adverse events. Generalized linear mixed models (Proc Glimmix procedures in SAS v9.3 with a random intercept for study site) will be applied to test for a difference between study arms for dichotomous (ART initiation, ART retention, TB treatment success, sputum smear conversion) and continuous (ART adherence, change in CD4+ count, TB treatment adherence) outcomes; frailty models (Proc Phreg procedures in SAS v9.3 with random intercept for study site) will be utilized for time to event analysis (time to ART initiation) to account for the clustering of characteristics that may occur among patients attending the same study site. These approaches will provide appropriate adjustments to the standard errors accounting for potential non-independence of observations (43). Models will include fixed effects for study condition, patient characteristics, time-varying adherence measures and CD4+ count (for change in CD4+ count) and random effects for site. Participants who transferred to another site before ART initiation will be censored, and death before ART initiation will be treated as a competing risk.

For the cost-effectiveness analysis, a model will be created to estimate the incremental cost of CIP relative to SOC. The costs will be composed primarily of the variable costs involved in training nurses and convening VHW, but will also include the costs of administering SMS messages and the fixed costs involved in administering the intervention. The incremental cost-effectiveness of CIP will be estimated as the ratio of the incremental costs to incremental effectiveness with effectiveness measured in terms of the study's primary outcomes.

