Our study has several strengths. First, the cluster-randomized approach permits the causal attribution of observed outcomes to the CIP by comparing them to the counterfactual scenario, while reducing selection bias (47). Second, the use of mixed methods (48, 49), whereby the collection and analysis of quantitative data is followed by the utilization of qualitative research tools in a sequential explanatory phase, will allow us to evaluate the acceptability and utilization of intervention components, and collect reasons for the lack of or late initiation of ART in TB/HIV patients. Third, the participatory approach, with meaningful stakeholder engagement in both the design and implementation phases, has fostered MOH ownership at the national and district levels, and will help to ensure the successful integration of study findings in policy and programmatic contexts. In addition, we are testing an innovative, multifaceted intervention that builds on the evidence base of prior scientific work, while addressing the diverse barriers to ART initiation and retention in TB/HIV patients. Finally, the selected study sites have adequate heterogeneity, covering facilities in both urban and rural locations in low-land, foothill, and mountainous areas, which will strengthen the external validity of findings.

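### ART retention, a primary outcome, is compared in a cohort selected after randomisation, so the unqualified intent-to-treat and causal statements do not hold for it

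*Protocol article*

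**What the plan says.** Under Primary and secondary endpoints the article states "Primary outcomes include: 1) ART initiation, 2) ART retention, and 3) TB treatment success". It then fixes the population of the second: "ART retention is defined as the percentage of measurement cohort participants who attended their 6-month clinic visit". A tolerance of one month applies to that visit, and the patient must also report taking ART. Patients who die or transfer count as not retained. Table 2 places ART retention, both adherence outcomes and CD4+ change in the measurement cohort. ART initiation and TB treatment success are placed in all TB/HIV patients.

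Entry to the cohort (Study participants, Measurement cohort) requires that the patient "initiated ART within 2 months of TB treatment initiation" and consents within 3 working days of starting ART. Under Recruitment, clinic nurses refer patients to the research assistant, and consecutive eligible consenting patients are enrolled up to a monthly quota per site. Facilities were assigned as whole units, with patients, health workers and study staff unblinded (Assignment to study arm). Nurses in CIP clinics encourage patients to start ART (Programmatic components of CIP).

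Data analysis says "An intent-to-treat analysis will be used". The only departure named is an additional as-treated analysis of adherence. The Discussion lists as a strength that the cluster-randomised approach "permits the causal attribution of observed outcomes to the CIP by comparing them to the counterfactual scenario, while reducing selection bias". The limitations paragraph does not mention that the retention population is formed after randomisation.

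**The concern.** Starting ART early is an event after randomisation, and the CIP exists to bring it about. If the CIP works on initiation, its cohort contains patients who would not have entered had their clinic been assigned to SOC. These added starters may be harder or easier to retain than patients who start under either condition. Referral by unblinded nurses and individual consent are further filters after randomisation.

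A difference in retention between the cohorts can therefore come from an effect of the CIP, from a difference in who was selected, or from both. The comparison could show benefit or harm where there is none, or hide a real effect. Adherence and CD4+ change have the same problem.

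**Working it through.** **Inputs from the article** (Sample size and power calculations): 12 clinics, 100 registered TB/HIV patients per clinic, 32 cohort members per clinic, ICC 0.05, two-sided alpha 0.05; initiation 40% vs 60%; retention 70% vs 90%. Six clinics per arm is inferred from the total of 12.

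**The plan's own figures first.**
- Cohort target: 12 × 100 × 0.40 × 0.80 = 384, as stated.
- Design effect: 1 + 31 × 0.05 = 2.55. Effective n per arm: 6 × 32 / 2.55 = 75.3.
- Power for 70% vs 90%, pooled normal approximation: SE under the null = √(2 × 0.8 × 0.2 / 75.3) = 0.0652; SE under the alternative = √((0.21 + 0.09) / 75.3) = 0.0631; z = (0.20 − 1.96 × 0.0652) / 0.0631 = 1.14; power 87.4%. The article states 87%.

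The power arithmetic is right. The problem is what is being compared.

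**Selection with no effect on retention.** Assumptions, none given by the documents: the 40% and 60% also hold for start within 2 months; the CIP adds starters and removes none; referral, consent and the quota do not depend on which kind of starter a patient is; patients who start under either condition are retained at 70% in both arms. The share of added starters in the CIP cohort is then 20/60, one third. With x the retention of added starters:

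CIP retention = (0.40 × 0.70 + 0.20 × x) / 0.60

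| x | CIP retention | Difference from 70% | Planned test rejects |
|---|---|---|---|
| 0.3 | 56.7% | −13.3 points | 39.6% |
| 0.5 | 63.3% | −6.7 points | 13.9% |
| 0.7 | 70.0% | 0 | 5.0% |
| 0.9 | 76.7% | +6.7 points | 15.2% |

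For x = 0.5: SE under the null = √(2 × 0.667 × 0.333 / 75.3) = 0.0768; SE under the alternative = √((0.21 + 0.232) / 75.3) = 0.0766. The two tails are at (0.0667 − 1.96 × 0.0768) / 0.0766 = −1.10 and (−0.0667 − 1.96 × 0.0768) / 0.0766 = −2.84, which sum to 13.9%.

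**Selection with a real effect.** If the CIP lifts patients who start under either condition from 70% to 90%, but added starters are retained at 50%, the CIP cohort shows (0.40 × 0.90 + 0.20 × 0.50) / 0.60 = 76.7% and power falls from 87% to 15%. At x = 0.7 it shows 83.3% and power is 49%.

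**Bounds.** With q the retention observed in the CIP cohort, retention in patients who start under either condition is at least (q − 1/3) / (2/3) and at most 100%. For q = 90% the lower bound is 85%; for 80% it is 70%; for 70% it is 55%.

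**An all-patient outcome.** Count a patient as a success if ART was started and the patient is in care on ART at month 6, with non-starters as failures. On the plan's figures this is 0.40 × 0.70 = 28% vs 0.60 × 0.90 = 54%. With design effect 1 + 99 × 0.05 = 5.95 and effective n 600 / 5.95 = 100.8 per arm, power is about 97%. If the CIP raises initiation only, it is 28% vs 0.60 × 0.70 = 42%, with power about 55%.

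**The case against.** Several counter-arguments carry weight.

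- **The 40% and 60% are not early-start rates.** They refer to ART started at any time during TB treatment, whereas cohort entry needs a start within 2 months. The article gives no early-start rate by arm. This stands: the one-third share is illustrative.
- **Intent-to-treat is not abandoned.** A reader might infer that patients are moved between arms or that the trial's causal claim fails as a whole. The documents do not support that. Facilities remain randomised, nothing suggests analysis outside the assigned arm, and deaths and transfers stay in as failures. The causal sentence describes the cluster design in general and is sound for the two primary outcomes measured in all registered patients.
- **Selection is partly limited.** Consecutive enrolment restrains selective referral, and the models include patient characteristics. Neither undoes conditioning on ART start, because the added starters may differ in ways not recorded.
- **An all-patient outcome measures something else.** It partly repeats ART initiation and can differ between arms with no effect on retention, as 28% vs 42% shows. A reader might infer that it should replace the primary outcome and would be well powered. The high power needs both planned effects, and replacement after data collection would be a considerable step. It belongs beside the cohort result.
- **Month-6 data may be thin.** Detailed visit and refill abstraction is described only for cohort members. This stands.

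A separate analysis plan may exist, but the article itself fixes the endpoint and its population, and no later modelling choice makes that a randomised comparison.

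**Conclusion.** The point holds. For ART retention, adherence and CD4+ change, the article's intent-to-treat and causal statements are wrong as written, because these outcomes are compared in groups selected after randomisation through an event the intervention targets. The structural point needs no numerical assumption.

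Its size does. Under the assumptions listed, added starters retained 20 points below or above the 70% base shift the contrast by 6.7 points either way, against a planned effect of 20 points, and roughly triple the false-positive rate. The documents do not say how added starters would be retained, so neither the direction nor the true size of the bias is known. A reader might infer that the CIP cohort must look worse because it takes in less motivated patients; nothing in the article establishes that. ART initiation and TB treatment success are not affected.

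**What to change.** 1. Label retention and the other cohort outcomes as conditional on early ART start and consent. Restrict the intent-to-treat and causal wording to outcomes measured in all registered patients, and add the selection issue to the limitations.
2. Report beside cohort retention, as the randomised comparison, the proportion of all newly registered TB/HIV patients who started ART and are in care on ART at month 6, with non-starters counted as failures. Take this from the registers and HIV care cards as far as they allow. State that it combines initiation with retention and is not a pure retention effect.
3. Give sensitivity bounds for the cohort contrast over a range of retention in added starters, using the early-start proportions observed in each arm in place of 40% and 60%.

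The cost is wording, one further analysis and a short sensitivity table. The downsides are that month-6 status outside the cohort rests on routine records without self-reported ART use and may be incomplete. Also, follow-up and record abstraction ended in March 2016 (Trial status), so the added analysis is specified after data collection and should be reported as such.
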